#### Objectives

To elaborate and optimise Project Respect and produce intervention materials in collaboration with the National Society for the Prevention of Cruelty to Children (NSPCC), four secondary schools, youth and policy stakeholders and the originators of effective US programmes informing our intervention.To adapt and cognitively test the SD and CADRI-s scales prior to piloting.To recruit six schools, undertake baseline CASI survey of two cohorts of students at the end of years 8 and 9 respectively plus online staff survey, and randomise four schools to receive the intervention and two to be usual-treatment controls (see Fig. 1).To ensure Project Respect is implemented for students in years 9 and 10, conduct process evaluation, and follow-up student CASI and staff online surveys 16 months post-baseline (start of years 10 and 11).To address the above research questions to inform progression to a phase III RCT.

**Fig. 1 Fig1:**
[figure not shown]
SPIRIT figure for pilot cluster randomised controlled trial of Project Respect

### Research design

#### Intervention elaboration and optimisation and cognitive interviewing to refine DRV scales

The core components of the intervention and the underlying theory of change have been informed by existing research, including studies on the Safe Dates and Shifting Boundaries interventions and existing systematic reviews as described above. Further work is required to elaborate the intervention methods and produce materials (manual, staff training and student curriculum), optimising these for use in the UK. This process will be led by the investigators and NSPCC working in close collaboration, and with the participation of students and teachers drawn from four secondary schools (different to those that will be involved in the pilot RCT), as well as the Advice Leading to Public Health Advancement (ALPHA) group [50]—a young people’s research advisory group—and policy stakeholders. We will elaborate and optimise the intervention through a systematic process involving review by researchers and NSPCC of existing systematic reviews and evaluation reports, elaboration of Project Respect methods and production of draft materials by NSPCC staff and the research team, consultation with stakeholders on the draft intervention materials via two facilitated workshops and web-based consultation and refinement of the draft intervention materials based on feedback. At the same time, we will adapt two existing DRV scales and refine the adaptations by conducting cognitive interviews with young people who are the same age as intended respondents. In cognitive interviewing, a qualitative method for pre-testing and improving survey questions, the focus is on the cognitive processes respondents use to answer survey items [51]. It aims to assess whether survey items are appropriate for their intended purpose [52], and we will use this approach to identify problems respondents encounter with survey items and to assess whether participants understand these items as intended. After adaptation, we will test these two scales in the pilot cluster RCT in order to determine which would be optimal for measuring DRV victimisation and perpetration as the primary outcomes in a phase III RCT. In these cognitive interviews, we will also pre-test selected items on attitudes and norms related to gender and DRV. Cognitive interviewing will occur in one of the schools taking part in elaborating the intervention and will involve eight male and eight female students. Students will complete paper questionnaires covering basic socio-demographics followed by the two DRV scales. They will then be interviewed and asked to ‘think aloud’ about how they answered the questions [53] with some probing [54] about comprehension, recall, judgement and response in relation to selected items [55].

#### Pilot RCT

We will then conduct a pilot cluster RCT (four intervention, two control schools; different to those involved in intervention elaboration and any subsequent phase III RCT), with an integral process evaluation and an embedded economic evaluation feasibility study. The research and intervention teams will be separately managed to ensure the evaluation is independent and that the proposed research does not distort intervention delivery. Although in the phase III RCT the intervention would be delivered over two academic years (targeting a single cohort of students progressing from year 9 to year 10 in this period), in this pilot the intervention will be implemented during one school year to two groups of students, those in year 9 and those in year 10. Curriculum lessons designed for each of these year groups will be piloted with the appropriate year group. One year of piloting is sufficient to assess feasibility and acceptability in order to address our research questions. Similarly, although a future phase III RCT would involve follow-up surveys at 28 months post-baseline, follow-up surveys in the pilot RCT will occur 16 months post-baseline. This timescale is sufficient to assess the feasibility of trial methods among participants of the same age as participants would be in a phase III trial at 28 months. Due to the sensitive nature of the baseline and follow-up student surveys, we will use a repeat cross-sectional rather than longitudinal design. The follow-up surveys will be conducted with the same two cohorts of students who took part in the baseline survey, but surveys will not be linked at the level of the individual. This design does not require that we link respondent names to the responses they submit, therefore protecting students’ anonymity.

The Standard Protocol Items: Recommendations for Intervention Trials (SPIRIT) figure (Fig. 1) outlines the key phases of the study. We provide a SPIRIT checklist in Additional file 1 [56, 57].

### Setting

The Project Respect intervention is intended for all mainstream secondary schools. There is no clear evidence that DRV among UK adolescents is associated with individual socio-economic status (SES) or school-level deprivation [27, 58]. Evaluating Project Respect in a sample of schools over-representing those in deprived areas would therefore unnecessarily undermine the generalisability of our findings.

#### Pilot trial inclusion criteria

Secondary schools (including free schools and academies) in southern England.

#### Pilot trial exclusion criteria

Private schools, PRUs and schools designed especially for students with learning disabilities.

### Population

As with similar previous studies [39, 40], Project Respect is a universal intervention for female and male students aged 13–15 years (in years 9 and 10 in UK schools). This age group is appropriate because this is the time when most dating behaviours begin, behavioural norms become established and DRV starts to manifest [30, 31]. Stakeholder consultations suggest provision to year 11 students is not feasible due to UK school exam timetables. In the pilot RCT, the intervention will run for 1 year only, targeting year 9 and 10 students, so that we may assess the intervention feasibility and acceptability.

#### Pilot trial inclusion criteria

Students nearing the end of years 8 and 9 at the time of the baseline survey

#### Pilot trial exclusion criteria

Students with severe cognitive limitations that would prevent them from understanding or consenting to take part in the research will not be included in the research. No other students in participating schools will be excluded from the study. Fieldworkers will support students who have mild learning difficulties or limited English proficiency to complete the questionnaire.

### Analytic sample and proposed sample size

The pilot RCT will focus on feasibility and no power calculation for this has been performed. Four schools implementing the intervention in the pilot trial balances the need to assess implementation in a diversity of schools while ensuring the pilot is small enough to be appropriate as a preliminary to a larger phase III RCT. The analytic sample for outcome assessment in the pilot will be a minimum of 1800 students at the ends of years 8 and 9 (aged 12/13 and 13/14 years) at baseline, with follow-up at 16 months. Data on fidelity and acceptability are intended to provide site-specific descriptive estimates rather than to be generalizable to a broader group of schools.

### Recruitment and randomisation

Four schools will be involved in intervention elaboration and optimisation, purposively sampled to vary by region and deprivation (as measured by the income deprivation affecting children index, IDACI). In the subsequent pilot RCT phase, three schools in southeast England and three schools in southwest England will be recruited; these schools will be different from those participating in optimisation. Schools taking part in the pilot RCT will be purposively sampled to ensure variation by deprivation and school-level value-added academic attainment, as approximate indicators of school capacity to deliver Project Respect.

We will recruit schools via letters and telephone calls to schools, local authorities, academy chains and school networks. Response rates will be recorded, as will any stated reasons for non-participation. After baseline CASI surveys with students at the end of years 8 and 9, schools will be stratified by region and randomly allocated 2:1 to intervention/control by the London School of Hygiene and Tropical Medicine (LSHTM) clinical trials unit (CTU). The 2:1 allocation will enable us to pilot randomisation while ensuring sufficient diversity among four schools for piloting the intervention. Retention of control schools will be maximised via £500 payment and feedback of survey data.

### Planned intervention

#### Intervention components

Project Respect is a manualised, multi-component school-based universal prevention intervention.

Table 1 summarises the Project Respect intervention according to the items included in the ‘Template for Intervention Description and Replication’ (TIDieR) checklist [59], and Fig. 2 presents the intervention's theory of change.

**Table 1 Tab1:** Description of the Project Respect intervention using TIDieR checklist items

TIDieR Item	Information on Project Respect intervention
Brief name	Project Respect
Why	We present the theory of change for Project Respect in Fig. 2. The intervention is underpinned by the theory of planned behaviour [93] and the social development model [94]. It is also supported by reviews which suggest that DRV interventions should challenge attitudes and perceived norms concerning gender stereotypes and violence as well as support the development of skills and control over behaviour [38]. Informed by the theory of planned behaviour, Project Respect will aim to reduce DRV by challenging student attitudes and perceived social norms about gender, appropriate behaviour in relationships, and violence; and by promoting student sense of control over their own behaviour. A key element of our theory of change is that attitudes and norms will be challenged not only via the student curriculum but also via actions at the level of the school environment to reduce gender-based harassment observable on the school site and increase school sanctions against gender-based harassment and DRV. Sense of control over behaviour will be promoted via the curriculum components focusing on communication and anger management skills. Informed by the social development model, Project Respect will enable student participation in curriculum lessons and leadership of campaigns in order to maximise learning, increase student bonding to school, and increase acceptance of school behavioural norms. The curriculum also aims to reduce DRV by promoting awareness of the Circle of 6 app [95] and local services, increasing the ability of those who experience DRV to seek support. Project Respect, like the earlier Shifting Boundaries intervention [40], includes a curriculum as well as school-elements. Informed by Shifting Boundaries, the Project Respect curriculum addresses gender roles and healthy relationships and uses hotspot mapping to inform changes in staff patrols of school premises. Informed by the earlier Safe Dates intervention [96], which is primarily curriculum-based, the Project Respect curriculum includes a focus on gender roles, conflict management skills, norms, and help-seeking and incorporates a student-led campaign component.
What materials	Schools allocated to receive the intervention will be provided with various resources. Schools will receive a manual to guide delivery of the intervention. School staff will be offered training (see below) and participants will receive slides to guide delivery of an all-staff training they deliver. Parents of students will be given written information on the intervention and advice on preventing and responding to DRV. Students will be given the opportunity to download the ‘Circle of 6’ app which helps individuals contact friends or the police if threatened by/experiencing DRV. Schools will be provided with written lesson plans and slides to guide delivery of a classroom social and emotional skills curriculum targeting students aged 13–15 years which includes a student-led campaign element.
What procedures	Project Respect is a multi-component school-based universal prevention intervention. The intervention aims to address DRV perpetrated by young people of all genders in heterosexual or same-sex relationships. School policies and rules will be rewritten to ensure that they aim to prevent and respond to DRV and gender-based harassment. Areas on the school site that are identified through student and staff mapping exercises as ‘hotspots’ for DRV and gender-based harassment will be patrolled by staff to prevent and respond to incidents. Responses will include appropriate sanctions for perpetration, support for victims and referral of victims or perpetrators to specialist services where necessary. The curriculum will include lessons that focus on (1) challenging gender norms; (2) defining healthy relationships; (3) inter-personal boundaries, consent, and mapping ‘hotspots’ for gender-based harassment and DRV on the school site; (4) how students can help a friend they are worried about, and empowering students to run campaigns challenging gender-based harassment and DRV; (5) communication and anger management skills relating to relationships; and (6) accessing local services relating to DRV and reviewing student-led campaign ideas. Learning activities will include: information provision; whole class discussions; video vignettes to help students identify abusive behaviours and relationships; quizzes; role plays and exercises; and cooperative planning and review of student-led campaigns. Schools that are randomly allocated to the intervention will be asked to continue with usual provision in addition to implementing the Project Respect intervention.
Who provides	School staff will implement the intervention with support from the NPSCC. Training will be provided by NSPCC for senior leadership and other key school staff to enable them to plan and deliver the intervention in their schools and review school rules and policies to help prevent and respond to DRV and gender-based harassment, and increase staff presence in ‘hotspots’ for these behaviours. Training will then be provided by these trained school staff for all other school staff in safeguarding to prevent, recognise and respond to gender-based harassment and DRV. The NSPCC will further support intervention delivery by offering advice sessions of up to one hour per week to intervention schools.
How	All intervention components will be delivered face-to-face and at the group level.
Where	All components will be delivered on school premises.
When and how much	Training by NSPCC will be provided in a 2–3-h session. Training within the school will be provided in a 60–90-min session. Policy review and hotspot mapping will occur in one or more school management meetings. School patrols will occur throughout the school year. The intervention curriculum will comprise six sessions in year 9 and two booster sessions for the same cohort in year 10, a relatively small number of lessons both years to ensure that the curriculum can be implemented in busy school timetables. As described in the ‘Research design’ section above, lessons in this pilot study will be delivered to students in years 9 and 10 during the same school year rather than to the same cohort over two years.
Tailoring	The intervention will not be tailored.
How well (planned fidelity assessment)	As described in the ‘Process evaluation’ section below, fidelity will be assessed via audio-recordings of the NSPCC-delivered and all-staff trainings, logbooks completed by teaching staff delivering curriculum sessions, structured observations of a randomly selected session per school of one curriculum lesson, interviews with the NSPCC trainer(s) and interviews with intervention school staff.

**Fig. 2 Fig2:**
[figure not shown]
Theory of change for Project Respect

#### Research and provider and roles

In close collaboration with the research team, NSPCC will lead the elaboration and optimisation of the intervention and the production of materials. In the delivery phase, NSPCC will work independently from the research team to train senior leadership and other key school staff in safeguarding to prevent, recognise and respond to gender-based harassment and DRV; to enable them to lead the intervention in their schools; to review school rules and policies to help prevent and respond to gender-based harassment and DRV; and to identify and increase staff presence in ‘hotspots’ for these behaviours. Trained school staff will then implement the school environment and curriculum components, cascading training in safeguarding to all staff.

#### Comparator

The comparator consists of schools randomly allocated to the control group. Control schools will not implement Project Respect, instead continuing with any existing gender, violence or sexual health-related provision. The study will include three additional activities to support all schools taking part: NSPCC will offer safeguarding officers of all schools a support session to prepare them in case the school experiences increased numbers of students seeking support as a result of the research or intervention (this will take place before the baseline surveys in case of such an increase immediately following baseline surveys; the training therefore takes place before randomisation); the research team will provide a short report to intervention and control schools about the prevalence of DRV reported in their schools; and NSPCC will brief its ‘Childline’ telephone helpline staff so that they are aware of the project in case the research or intervention results in students contacting them. While these activities mean the experience of control schools will differ slightly from treatment as usual, we feel this measured response is essential to fulfil our duty of care to trial participants while not excessively distorting the nature of the comparator. The nature of the comparator will be assessed by examining the sexual health education provision in and around control schools at baseline.

### Outcome measures

In the pilot RCT, the primary outcome will be whether progression to a phase III RCT is justified in terms of the pre-specified criteria listed in research question 1. The pilot RCT will also determine which of two existing DRV scales will be used to measure the primary outcomes of DRV victimisation and perpetration in a phase III trial.

All measures of primary and secondary outcomes and mediators that would be examined in a phase III RCT will also be assessed for reliability in this pilot.

The twin primary outcomes in a phase III RCT would be binary measures of DRV victimisation and perpetration, measured using self-reports rather than via routine data. This is because most experiences of DRV will not result in notifications to the school, police or NHS [43] and our intervention is likely to increase rates of such notifications with the risk of ascertainment bias. While our intervention might also result in increased self-reports, this reporting bias will be minimised by use of a validated and reliable measure comprising items focused on specific behaviours. As there is currently no clear evidence as to whether the SD or CADRI-s measure is the optimal scale to assess DRV victimisation/perpetration in this population, we will adapt and test these measures in this pilot to determine which is most suitable in the UK context.

The SD measure of dating violence is based on self-reported perpetration and victimisation of psychological abuse and of physical and sexual violence in the previous year. Participants are asked ‘How often has anyone that you have ever been on a date with done the following things to you?’ Response options range 0–3, indicating frequency. Items are summed and then recoded 0–3 indicating overall degree of abuse. Psychological abuse is assessed in terms of 14 acts (Cronbach’s alpha = 0.91 for victimisation and 0.89 for perpetration) [47, 60]. Physical and sexual violence are assessed in terms of 18 acts, of which 6 indicate serious physical violence and 2 indicate forced sexual acts (Cronbach’s alphas for perpetration of moderate physical violence = 0.92, for severe physical violence = 0.89 and for sexual violence = 0.86). For victimisation, Cronbach’s alphas are respectively 0.90, 0.86 and 0.74 [47]. The SD measure is one of the most commonly used in research on adolescent dating violence [61] and correlates with poor mental health and various health risk behaviours including other forms of youth violence and substance use [23, 62, 63]. Reliability has been examined in multiple studies of adolescents, but not in the UK to date. We will add introductory text to clarify our interest in both on- and off-line behaviours. Our primary outcome will examine categorical measures of DRV perpetration and victimisation, while secondary outcomes will examine each subscale.

The CADRI measure comprises 92 items assessing DRV victimisation and perpetration over the past year. Subscales cover emotional abuse, relational abuse, controlling behaviours, physical violence and non-consensual sexual activities. Items are rated on a 4-point scale according to frequency, allowing generation of a binary measure of prevalence or a quantitative measure of frequency created from the summed score divided by the number of items. Research has found that DRV as measured via the CADRI scale is correlated during adolescence with early sexual debut, unsafe sex, violence and suicidal ideation [64]. The CADRI instrument has been used in research with young people in the USA, Canada [65, 66] and Spain [67], but not in the UK to date.

The use of the CADRI measure within trials is problematic due to its length. A short 10-item version of the CADRI, the CADRI-s, has been developed and piloted among school-based samples of students in 9th–12th grade and in at-risk samples in Canada. The new measure was found to be slightly less sensitive than the full questionnaire but to have good reliability, fit and convergent validity with the full measure [68]. We plan to further assess this short version. We will modify the scale by adding text clarifying our interest in both on- and off-line behaviours and adding two items from the original CADRI measure to assess experience of controlling behaviours. The developers of the SD and CADRI-s have permitted our use and modification of these measures. We propose to use the pilot RCT to refine the two existing measures, cognitively test these to inform further refinements and then pilot the measures and assess completion rates, inter-item reliability (using Cronbach’s and ordinal alphas) and fit (using confirmatory factor analysis).

Informed by our theory of change, secondary outcomes in a phase III RCT will include the following, which we will assess for reliability in this pilot trial:DRV frequency of victimisation and perpetration (using the SD and CADRI-s measures).Short Warwick-Edinburgh Mental Well-Being Scale (SWEMWBS). This is a 7-item scale designed to capture a broad concept of positive emotional well-being including psychological functioning, cognitive-evaluative dimensions and affective-emotional aspects [69]. Items are rated on a 5-point scale: none of the time, rarely, some of the time, often, or all of the time. Responses are scored and aggregated to form a ‘well-being index’ with a higher score representing greater well-being [69].Paediatric quality of life inventory (PedsQL) version 4.0. This is used to assess overall quality of life. The 23-item PedsQL [70] has been shown to be a reliable and valid measure of quality of life in normative adolescent populations. It consists of 23 items representing 5 functional domains—physical, emotional, social, school and well-being—and yields a total score, two summary scores for ‘physical health’ and ‘psychosocial health’, and three subscale scores for ‘emotional’, ‘social’ and ‘school’ functioning.Sexual harassment. Two new items measuring experience of sexual harassment (1) overall and (2) in school, drawing on a widely accepted definition of what constitutes sexual harassment [71].Strengths and Difficulties Questionnaire (SDQ). This is a brief, validated instrument for detecting behavioural, emotional and peer problems and pro-social strengths in children and adolescents. It comprises 25 items across five scales assessing emotional symptoms, conduct problems, hyperactivity/inattention, peer relationship problems and prosocial behaviour. A higher total problems score indicates greater problems [72].Self-reported sexual health. We will examine pregnancy and unintended pregnancy (initiation of pregnancy for boys) and sexually transmitted infections, age of sexual debut, partner numbers, and use of contraception at first and last sex using measures from previous RCTs [73, 74].Self-reported use of primary care, accident and emergency, other service in past 12 months.Self-reported contact with police [75].School attendance and educational attainment via routine school-level data on half-days absent and General Certificate of Secondary Education (English secondary school qualification) performance for the trial cohorts.

Informed by the intervention’s theory of change, we will also examine the following mediators (to be assessed for reliability in this pilot trial):Social norms and gender stereotyping. We will use a modified version of a multi-item subscale developed by Foshee [23] measuring acceptance of prescribed norms (acceptance of dating violence under certain circumstances) using a 4-point Likert scale format, and adapt these items to measure injunctive norms (beliefs about others’ attitudes towards dating violence). Items are averaged to create a composite score [23]. We will use a modified version of items used by Cook-Craig et al. to measure descriptive norms (beliefs about whether DRV is common) [76]. We will measure gender stereotyping using a modified version of the 16-item Attitudes Towards Women Scale, which has high reliability and uses a 4-point Likert scale format [77]. We will adapt these items to measure injunctive norms (beliefs about others’ attitudes towards gender stereotypes).Self-reported awareness of services, and help seeking for victims and perpetrators. We will assess these via existing single-item self-report measures [23].Communication and anger management. We will assess these using the Modified Sexual Communication Survey (MSCS) and SDQ respectively. MSCS measures open sexual communication with a current or potential partner [78]. The scale includes 21 eight-point Likert scale items examining frequency and has excellent reliability [79, 80].Dating violence knowledge. This will be measured using a modified version of a reliable multi-item scale involving true/false questions on help-seeking and definitions [40].Downloading and use of the ‘Circle of 6’ app will be measured by a new single-item measure.

To ensure student surveys are age-appropriate, items with sensitive sexual content will be excluded at baseline but included at 16-month follow-up.

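### The Safe Dates measure is defined as covering the previous year, but the question quoted for it puts no time limit on the acts

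*Protocol article*

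**What the plan says.** All the wording is in the Outcome measures section of the protocol article. SD is described as based on "self-reported perpetration and victimisation of psychological abuse and of physical and sexual violence in the previous year". The next sentence gives the question put to participants: "How often has anyone that you have ever been on a date with done the following things to you". The one change named for the SD text is "We will add introductory text to clarify our interest in both on- and off-line behaviours".

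The rival instrument is introduced as follows: "The CADRI measure comprises 92 items assessing DRV victimisation and perpetration over the past year". The version to be piloted is the short one: "A short 10-item version of the CADRI, the CADRI-s, has been developed and piloted". No recall period is given separately for it. Both scales may still change: "We propose to use the pilot RCT to refine the two existing measures, cognitively test these to inform further refinements".

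Four other statements matter:
- Research design places follow-up at 16 months in the pilot and 28 months in phase III, with no individual linkage between waves.
- Outcome measures makes binary victimisation and perpetration the twin phase III primary outcomes, with SD or CADRI-s as the instrument.
- Research question 4 compares pilot prevalence and ICC with the literature to inform the phase III sample size.
- Research question 2 chooses between the scales on completion, inter-item reliability and fit.

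**The concern.** Two adjacent sentences give SD different time frames: one year in the definition, none in the question. A binary outcome without a time limit stays positive once it has become positive. Students are 12–14 at baseline, the age at which the Background says DRV starts to appear, so some acts before randomisation are plausible. The intervention cannot prevent those acts, and they would be counted in both arms at follow-up.

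Two uses of the data would suffer. An effect on an SD-based phase III outcome would be pulled towards no effect. In the pilot, the check under research question 4 would set SD prevalence and ICC without a recall limit against past-year figures. Any SD–CADRI difference in prevalence would likewise mix recall period with scale content.

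**Working it through.** **1. Wording side by side.**

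| Item | Time frame of the acts |
|---|---|
| SD, as defined | previous year |
| SD, as asked | none; *ever* describes which dating partners count |
| SD, named change | on- and off-line behaviour only |
| CADRI (92 items) | past year |
| CADRI-s | not stated; inferred from the parent scale |

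**2. Windows.** A 12-month window at follow-up runs from 16 − 12 = month 4 to month 16 in the pilot, and from 28 − 12 = month 16 to month 28 in phase III. Both lie wholly after baseline, so the past-year definition excludes pre-baseline acts. The printed stem has no lower bound and does not. Without linkage, a student's baseline answers cannot be used to remove them.

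**3. Size.** The article gives no power or sample size figure that depends on this, so there is nothing to reproduce. The illustration below rests on assumptions that are not in the article: a share *b* with DRV before baseline (10–20%), a share *p* with new DRV after baseline in controls (15–25%), independence of the two, and a true risk ratio of 0.75 on new DRV.

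- Any-time prevalence, control: 1 − (1 − b)(1 − p)
- Any-time prevalence, intervention: 1 − (1 − b)(1 − 0.75p)
- n per arm: (1.960 + 0.842)² × [p₁(1 − p₁) + p₂(1 − p₂)] / (p₁ − p₂)², for two-sided 5%, 80% power, no clustering

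Mildest corner, b = 0.10 and p = 0.25:
- Control 1 − 0.90 × 0.75 = 0.325; intervention 1 − 0.90 × 0.8125 = 0.269; risk ratio 0.827.
- n per arm is 683 for new DRV only (0.25 v 0.1875) and 1,032 for any-time DRV, a ratio of 1.51.

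Worst corner, b = 0.20 and p = 0.15:
- Control 1 − 0.80 × 0.85 = 0.320; intervention 1 − 0.80 × 0.8875 = 0.290; risk ratio 0.906.
- n per arm is 1,269 for new DRV only (0.15 v 0.1125) and 3,694 for any-time DRV, a ratio of 2.91.

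| b | p | Observed RR | n ratio |
|---|---|---|---|
| 0.10 | 0.15 | 0.856 | 1.85 |
| 0.10 | 0.25 | 0.827 | 1.51 |
| 0.15 | 0.15 | 0.885 | 2.35 |
| 0.15 | 0.25 | 0.853 | 1.81 |
| 0.20 | 0.15 | 0.906 | 2.91 |
| 0.20 | 0.20 | 0.889 | 2.43 |

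Over the stated ranges the observed risk ratio is therefore about 0.83–0.91, and the unclustered sample size rises 1.5 to 2.9 times.

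**4. Sensitivity.** Taking new DRV at 12–48% (the spread of the article's English prevalence figures), prior DRV at 5–20%, and a pooled-variance formula gives an observed risk ratio of about 0.78–0.92 and a sample size 1.1 to 3.4 times larger. Those prevalences refer to 14–17-year-olds who report a relationship, so they too are only illustrative here.

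**The case against.** The strongest reply is that the article states the window explicitly and the stem does not contradict it outright. *Ever* attaches to the partner, not to the act. One victimisation question is quoted, not the questionnaire, and a time limit could sit in instructions that a journal article would not reproduce. Both scales were also to be adapted and cognitively tested, with probing on recall, so the printed stem need not be final. All of this stands. A reader might infer that SD is an explicit lifetime measure, or that trial data already count pre-baseline violence. The document does not show either. What it shows is a stem without the limit that its definition requires, and no stated plan to add one.

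The stakes are also narrower than they may appear. Progression is the pilot's primary outcome, and its criteria do not use DRV prevalence. The scales are compared on completion, reliability and fit. If both perform well, CADRI-s is chosen, so dilution in phase III arises only if SD is used there. The article itself calls the prevalence and ICC check a more qualitative assessment. These limits hold. They do not remove the problem for that check or for SD as a candidate primary outcome.

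Finally, past year is stated for the full CADRI only, so a mismatch with CADRI-s is an inference.

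**Conclusion.** The point holds as an inconsistency between definition and question. Used as printed, the SD stem would not give the past-year outcome that the article describes and would admit pre-baseline acts that unlinked surveys cannot separate. On the assumed inputs, a true risk ratio of 0.75 would appear as about 0.83–0.91 and require 1.5 to 2.9 times the unclustered sample size. The size rests on assumed prevalences, independence of prior and new DRV, and the stem being fielded without a limit elsewhere in the instrument.

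What is affected is an SD-based phase III outcome and the comparability of SD prevalence and ICC, both with past-year figures and with the past-year CADRI. The document does not support reading this as a threat to the progression decision. Nor does it show that SD data without a recall limit would be unusable for choosing between the scales.

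**What to change.** Put *in the past 12 months* in the SD stem or its introductory text, for both victimisation and perpetration, and state the matching recall period for CADRI-s. If the fielded questionnaire already carries the limit, say so and quote it.

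If any wave was collected without the limit, keep it for completion, reliability and fit. Label its SD prevalence and ICC as having no recall limit, and do not compare them with past-year figures or directly across waves.

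The cost is one phrase and a small departure from the original stem; the scale developers have already permitted modification. If baseline used the unlimited stem, changing it at follow-up reduces comparability of SD between waves, which matters for a repeat cross-sectional analysis. Timing may also limit the remedy. Baseline enrolment began in June 2017, so 16 months later is about October 2018. That is after submission in May 2018 but before publication in January 2019. If follow-up was already complete, the labelling rule applies to the pilot data and the wording change to phase III.
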